## Abstract

**Background:**

A strong increase in smoking is noted especially among adolescents. In the Netherlands, about 5% of all 10-year olds, 25% of all 13-year olds and 62% of all 17-year olds report ever smoking. In the U.S., an intervention program called 'Smoke-free Kids' was developed to prevent children from smoking. The present study aims to assess the effects of this home-based smoking prevention program in the Netherlands.

**Methods/Design:**

A randomized controlled trial is conducted among 9 to 11-year old children of primary schools. Participants are randomly assigned to the intervention and control conditions. The intervention program consists of five printed activity modules designed to improve parenting skills specific to smoking prevention and parent-child communication regarding smoking. These modules will include additional sheets with communication tips. The modules for the control condition will include solely information on smoking and tobacco use.

Initiation of cigarette smoking (first instance of puffing on a lighted cigarette), susceptibility to cigarette smoking, smoking-related cognitions, and anti-smoking socialization will be the outcome measures. To collect the data, telephone interviews with mothers as well as with their child will be conducted at baseline. Only the children will be examined at post-intervention follow-ups (6, 12, 24, and 36 months after the baseline).

**Discussion:**

This study protocol describes the design of a randomized controlled trial that will evaluate the effectiveness of a home-based smoking prevention program. We expect that a significantly lower number of children will start smoking in the intervention condition compared to control condition as a direct result of this intervention. If the program is effective, it is applicable in daily live, which will facilitate implementation of the prevention protocol.

**Trial registration:**

Netherlands Trial Register NTR1465

## Background

A strong increase in smoking is noted especially among adolescents. Between 80,000 and 100,000 of young adolescents worldwide start smoking each day [1]. In the Netherlands, 40% of youths between the ages of 10 and 19 reports ever smoking [2]. Findings on early onset and later cigarette use suggest that those who initiate smoking in childhood are more likely to report advanced levels of smoking and nicotine dependence in late adolescence and (early) adulthood [3-6]. The consistency of findings regarding the effects of early initiation on future smoking has led investigators to advocate for a delay in the age of onset as an important strategy for preventing tobacco use.

One potential powerful tool to lower the prevalence of youth smoking and to delay the age of onset is the implementation of effective prevention programs. In the past decade, various prevention programs have been implemented primarily at secondary schools (e.g., [7]). Programs targeting on early adolescents need to be improved to be more effective [8,9]. One of the reasons that current school-based prevention programs have had little sustained effect on smoking rates is - in our opinion - the general disregard of the role of parents in preventing youth smoking onset.

Recent studies have shown that parental smoking [10], general parenting style, and parental anti-smoking socialization (e.g., [11-14]) predict smoking experimentation, progression to advanced stages of smoking, and even smoking cessation [15]. In the last five years, prospective studies have extensively studied the influence of parents on child smoking in the Netherlands. These studies generally show that parents are the primary socializing agents. Parents affect the norms of children with respect to smoking by communicating constructively about smoking-related issues, setting household rules against smoking, acquiring additional smoking-related knowledge, and monitoring their children's activities. In turn, this lowers the odds of children experimenting with smoking [11,13,16-18]. In addition to the direct influence of parents on adolescent smoking initiation, parents can also influence their children indirectly through cognitions. Anti-smoking specific parenting practices have been found to be related to adolescents' smoking-specific cognitions (i.e., social norm, self-efficacy, and attitudes [13,19], and these smoking-specific cognitions have been found to mediate the relation between parental smoking and initiation of smoking [11,17]. Considering these findings, we expect that smoking-specific cognitions will mediate the association between parenting practices and smoking initiation.

There is overwhelming empirical evidence that parents can prevent their children from smoking by engaging in anti-smoking socialization. However, no effective prevention program for parents of children aged 9-11 years old has been tested and implemented in the Netherlands. In the U.S., Jackson and Dickinson [20,21] have developed a highly innovative and successful prevention program for smoking parents of primary school children named 'Smoke-free Kids.' Smoke-free Kids is a structured program focused on anti-smoking socialization that can be conducted at home, which means that parents and children can go through these activities in their own time. Using communication, rule setting, monitoring, guided experience, and other methods of child socialization, parents can influence children's perceptions regarding the prevalence of smoking, the acceptability of smoking, and the personal and social consequences of smoking [22].

A randomized control trial conducted over a period of 24 and 36 months has provided strong evidence for the preventive effects of the Smoke-free Kids program on child smoking initiation [21]. Specifically, analyses showed that exposure to the program reduced the likelihood of children's smoking initiation at follow-up (24-months later). While 19% of children in the control condition initiated smoking by grade 6, only 12% of children in the intervention condition had done so (OR = 2.16; 95% CI 1.39 to 3.37, p < .001).

### Asthma

Health effects of smoking initiation are more profound on adolescents with asthma compared to adolescents without asthma. People with asthma who smoke are more likely to develop lung diseases and COPD [23] over time compared to those who do not smoke. Worldwide, the prevalence of asthma varies across countries and age groups. The prevalence of asthma among children aged 7-9 years old ranges from 0% to 20.3% and among 13-14 year olds from 0.1% to 16% (ISAAC study: [24]). Our institute is one of the participating collaborating parties in the ISAAC study, the worldwide epidemiological project on the prevalence of asthma and asthmatic symptoms. According to Dutch data collected from 10,087 adolescents aged 12-14 years old, 13% of the participants reported lifetime asthma and 7% reported asthmatic symptoms in the last 12 months [25]. Although one might expect that- due to the long-term negative consequences of cigarette use - adolescents with asthma would be less likely to start smoking, the contrary seems to be true (see also [26,27]). The prevalence of regular smoking among adolescents with asthma is as high as among their non-asthmatic peers [28]. In addition, adolescents with asthma are more likely to have parents who smoke than adolescents without asthma [29]. Smoking parents are less involved in anti-smoking socialization than non-smoking parents [22]. Therefore, it is important to involve this vulnerable group in smoking prevention and to examine whether the effects of the Smoke-free Kids program are different for children with and without asthma.

### Aim and hypotheses

The primary aim of the study Smoke-free Kids is to assess the effectiveness of this prevention program among children aged 9-11 years old in the Netherlands. Both short-term (after 6 months) and long-term (12, 24, 36 months) effects of the intervention will be tested. Two hypotheses will be tested. First, in line with the U.S. findings, we expect that the program will lead to lower likelihood of children's smoking initiation. Specifically, we expect that children in the intervention condition, relative to controls, will be less likely to engage in smoking at follow-up based on the findings of Smoke-free Kids in the U.S. We will test whether the effects of the intervention program are different for children with asthma. Second, we expect that the program will lead to significant increases in anti-smoking socialization of children. Specifically, we expect that parents included in the intervention program (as compared to controls) (a) will be more engaged in constructive communication on smoking topics, (b) will have more confidence in discussing smoking matters and greater self-efficacy to prevent their children from smoking, (c) will set and keep stricter household rules against smoking and establish a non-smoking contract with their children, and (e) will be more likely to monitor children's and peers' smoking-related activities.

## Methods/Design

### Study Design

The program Smoke-free Kids is a 3-year randomized controlled trial with two arms, an intervention and a control condition, testing the effects of an intervention program consisting of five activity modules. Participants consist of 1479 mothers (and their children): 729 in the intervention and 750 in the control condition. To select the eligible sample, randomization takes place at school level, to avoid contamination between conditions, after the initial recruitment and participant selection. After informed consent, enrollment in the trial, and baseline assessment, families will receive one of the five program modules every four weeks by mail. The modules for the intervention condition will consist of activities (such as games, scripted role-plays, contests, and interviews) designed to increase communication between mother and child. Mothers will be instructed to read the modules and to perform these activities together with their child. The intervention condition will also receive a booster module 12 months after the baseline to reinforce the skills learned from the earlier modules. Families in the control condition will receive modules containing only of factual information about smoking. Hence, these mothers will not be explicitly encouraged to communicate about the modules with their child.

Assessments in both intervention and control condition will be conducted at baseline, after six months (after completing the intervention), 12, 24, and 36 months (see Figure 1).

**Figure 1 F1:**
[figure not shown]
**Study design**.

After 36 months of follow-up, each family will receive €10 for participation in all measurements, and five traveler's cheques of €1000 will be raffled among these families. Children will receive little gifts after different measurement (e.g., pen & memo pad, magnet stickers, Frisbees) to thank them for participating in the study.

### Participants

#### Recruitment

Families are recruited from primary schools, media, and health professionals. Specifically, primary school boards are asked to distribute letters to all children aged 9-11 years old and to request that children give this letter to their parents. This letter includes information about the study and inquires whether parents want to be involved in our study. If parents agree to participate, they can provide their contact information by filling out a short screening self-administered questionnaire (that includes items assessing parental smoking status and possible asthmatic symptoms of the child) and return it in the enclosed envelope. It is also possible to register online via a secured webpage. To recruit children with asthmatic symptoms, several local and national newspapers, a local television station, and different health related prevention websites (e.g., Dutch Asthma Foundation, Dutch Institute for Smoking Prevention) agreed to assist in announcing the study on a population level. Furthermore, health professionals (i.e., general practitioners, pharmacist, and lung specialists) are requested to place posters with accompanying flyers in their waiting rooms.

#### Eligibility Criteria

Eligibility is determined in two steps; first based on a short screening self-administered questionnaire completed by the parents, and second based on the baseline telephone interview. Inclusion criteria for the present study are; children have to be aged between 9-11 years old and should not have initiated smoking yet, participating adults have to be the mother or a female guardian, and both adult and child need to be competent in reading and speaking Dutch. Furthermore, only one child per household is eligible to participate. To test the moderating effect of asthma, we also needed a subsample (*n *= 200) of children with asthmatic symptoms. Written informed consent from participating families will be obtained upon enrollment. The ethics committee of the Faculty of Social Sciences at the Radboud University Nijmegen approved the study's protocol.

In this study, we will focus on 9 to 11 year old children because at this age, children start to become increasingly interested in smoking issues (see [30]), but generally do not smoke yet. The prevalence of lifetime smoking among this age group is low (< 2%) [31], making it an important target group for primary prevention. Furthermore, this age group consists of children prior to the phase in which they enter pre-puberty. This is a period characterized by increasing conflicts with parents, particularly with mothers [32], leading to less conformity and openness, although children are still responsive to the influence of parents [21].

We have decided to target mothers rather than fathers for the following reasons; (a) if parents are divorced, children live mostly with their mothers [33], (b) on an average, children spend more time with their mothers than with their fathers, which gives mothers the practical advantage of having more time to deliver the anti-smoking socialization program to their children, [34] (c) women are generally more likely than men to enroll in health-related programs, (d) the U.S. trial also included only mothers, so including mothers would increase comparability of findings [20,21], and (e) given the plausibility that program effects would differ by parent's gender, including fathers would substantially increase the size and costs of the proposed trial.

#### Randomization

Randomization occurs at the school level to avoid contamination between conditions. Thus, clusters of children from one school are allocated to either the intervention or the control condition. An independent statistician performed the allocation and stratified participants by school and number of children with asthma after the baseline assessment.

### Sample Size Calculation

Based on the findings from the U.S. trial, we expect a 10% difference in smoking initiation rates between the intervention and control conditions. Equal cell sizes are assumed for study cells and power of .80 was targeted. The primary hypothesis will be tested at an overall two-sided significance level of 0.05. We used the general-purpose statistical software package Stata to calculate the estimated sample sizes for two-sample comparison of proportions. Based on the U.S. data and the prevalence of smoking in 12 to 14 year olds (age of the children at 36-months follow-up), which is around 30%, we would need 428 children per condition. In these power analyses, we corrected for the fact that data are clustered (children are nested within schools) and the fact that we will apply multiple imputation in the case of missing data. Thus, 856 children (and mothers) would be included to test the effectiveness of Smoke-free Kids. A sub-goal of the study is to examine whether there is any difference between the children with and without asthma or asthmatic symptoms. To test the moderating effect of asthma or asthmatic symptoms, we will include a subsample of 200 children with asthma or asthmatic symptoms. This allows us to test whether the effect of the intervention is different for children with asthma. Eventually, the study is over-enrolled. Overall, a total of 1479 children (and mothers) will participate in the study: 1399 never smokers and 80 ever smokers. The asthmatic subsample includes approximately 239 children whose mothers reported their child to have had an asthmatic period at least once in their lives. This allows us to test whether the effect of the intervention is different for children with asthma. Moreover, having 623 additional participants allows us to do complex analyses and to test several other moderators and mediators. In accordance with the intention-to-treat philosophy, all children randomized to one of the conditions are included in analyses to test the study hypotheses.

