### Outcomes

The primary outcome, initiation of cigarette smoking, has been defined as puffing on a lighted cigarette for the first time. Secondary outcome measures are general parenting dimensions like monitoring, psychological control, manipulative control, support and responsiveness (e.g., [41-44]), as well as smoking-specific parenting, such as house rules on smoking, non-smoking agreement, warnings about consequences of smoking, frequency and quality of communication on smoking matters, and reactions on experimentation with smoking (e.g., [11,17,19,45-47]). Other outcomes are susceptibility to cigarette smoking, defined as the lack of a firm commitment against cigarette smoking [9,48], child smoking-related cognitions, such as expectancies concerning self-efficacy [49], and social norms [13] which have been shown to be related to smoking initiation [12,28] and attitude [13]. Asthma symptoms will be identified using an extended version of ISAAC's asthma questionnaire [50]. In addition, children with asthmatic symptoms will be phenotyped using lung function measurement. The Strengths and Difficulties Questionnaire (SDQ) [51] will be used as a behavioral screening instrument for early detection of psychological problems. Psychological problems are associated with problem behaviors like smoking (e.g., [52]).

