### Statistical analyses

The main comparisons of study conditions with respect to the distribution of time until first instance of smoking will be based on survival analysis methods. All available data for participants who are randomized but lost to follow-up will be used in the survival analysis. This way, if a participant is not able to be located after the first year, for example, the data collected from the participant up to one year will be used in estimating the intervention effect and will contribute to the time trend estimates up to a year. Survival analysis is selected as the primary analysis in part because it easily incorporates censored observations. Logistic regression models will also be used to test how the intervention is related to susceptibility of smoking in originally abstinent children. Mplus analyses will be used to deal with missing data at the subsequent waves and to control for the clustered data (e.g., the fact that we randomize on school level) (see [53]).

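### The all-randomised analysis rule takes in 80 ever smokers who cannot newly have the primary event (first puff), so the primary analysis set contradicts the eligibility criterion and the outcome definition

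*Protocol article*

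**What the plan says.** All references are to the protocol article.

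- **Eligibility Criteria:** "children have to be aged between 9-11 years old and should not have initiated smoking yet". Eligibility is checked in two steps, first on a parent-completed screening questionnaire and "second based on the baseline telephone interview".
- **Study Design:** 729 families are in the intervention condition and 750 in the control condition, 1479 in all.
- **Sample Size Calculation:** the same 1479 are described as "1399 never smokers and 80 ever smokers". Citing intention to treat, the section ends by saying that "all children randomized to one of the conditions are included in analyses to test the study hypotheses".
- **Aim and hypotheses:** the first hypothesis concerns smoking initiation, the second anti-smoking socialization.
- **Outcomes:** the primary outcome, initiation, "has been defined as puffing on a lighted cigarette for the first time".
- **Statistical analyses:** the main comparison is a survival analysis of time to the first instance of smoking, with no stated limit on baseline smoking status. The logistic models, by contrast, address "susceptibility of smoking in originally abstinent children".
- **Randomization:** allocation was by school, stratified by school and "number of children with asthma after the baseline assessment". Smoking status is not named as a stratification factor.

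**The concern.** A child who has already puffed on a cigarette is not at risk of doing so for the first time. The eligibility rule would keep such children out, yet 80 are in the allocated sample, and the one explicit statement about who is analysed keeps them in the test of the initiation hypothesis. The limit to abstinent children is written for susceptibility and not for the primary outcome, so a reader cannot assume that it carries over.

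An analyst who follows the text has two ways to keep the 80 in: count them as events that happened before allocation, or as children followed without ever having the event. Neither estimates the effect on initiation. Leaving them out would estimate it, but departs from the written rule. At stake are which children form the primary analysis set and some dilution of the estimate.

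**Working it through.** **1. Are the 80 among the allocated children?** 729 + 750 = 1479 and 1399 + 80 = 1479, so yes. Their share is 80/1479 = 5.4%.

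**2. The plan's own sample size.** Inputs from Sample Size Calculation: about 30% in controls, a 10% difference (read as absolute, so 20% under intervention), two-sided 0.05, power 0.80, equal arms. With

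n = [1.96·√(2·p̄·(1−p̄)) + 0.842·√(p1(1−p1) + p2(1−p2))]² / (p1−p2)²

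and p̄ = 0.25, n = (1.200 + 0.512)²/0.01, which gives 294 per arm (313 with continuity correction). The stated 428 therefore implies a combined inflation for clustering and missing data of 428/294 = 1.46 (428/313 = 1.37 with the correction). The components are not given, so 428 can be neither confirmed nor refuted. Below, inflation is varied from 1 to 2.

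**3. Effect on the planned difference.** Assume 30% versus 20% among never smokers, with the 80 split in proportion to arm size. The never-smoker share is 1399/1479 = 0.946.

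| Handling of the 80 | Control | Intervention | Difference |
|---|---|---|---|
| Left out | 30.0% | 20.0% | 10.0 points |
| Coded as events | 0.946·0.30 + 0.054 = 33.8% | 0.946·0.20 + 0.054 = 24.3% | 9.46 points |
| Coded as non-events | 0.946·0.30 = 28.4% | 0.946·0.20 = 18.9% | 9.46 points |

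On the ratio scale the codings differ. The risk ratio is 0.20/0.30 = 0.67 with the 80 left out, 0.243/0.338 = 0.72 as events, and unchanged at 0.67 as non-events.

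**4. Power.** Two-proportion normal approximation, with the number per arm (699.5 without the 80, 739.5 with them) divided by the inflation factor:

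| Inflation | 1399 never smokers | All 1479, as events | All 1479, as non-events |
|---|---|---|---|
| 1.0 | 0.991 | 0.980 | 0.990 |
| 1.37 | 0.960 | 0.930 | 0.956 |
| 1.46 | 0.948 | 0.914 | 0.945 |
| 2.0 | 0.864 | 0.810 | 0.858 |

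Dropping the 80 never lowers power here, and every figure exceeds 0.80.

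**5. Unequal split by arm, coded as events.** The article does not give the split of the 80, so 30/50 is illustrative. With 30% initiation among never smokers in both arms (no true effect):

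- 30 intervention, 50 control: (30 + 0.3·699)/729 = 32.9% versus (50 + 0.3·700)/750 = 34.7%, an apparent difference of 1.8 points favouring intervention.
- 50 intervention, 30 control: (50 + 0.3·679)/729 = 34.8% versus (30 + 0.3·720)/750 = 32.8%, an apparent difference of 2.0 points favouring control.

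With a true 30% versus 20%, the same splits give 11.4 and 7.3 points, about 2 points either side of 9.46. If children were allocated independently, 80·729/1479 = 39.4 would be expected in the intervention arm with a standard deviation of about 4.5, so 30 or fewer has a probability of about 2%. Allocation by school makes such a split likelier than that.

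**The case against.** The strongest defence is that the named primary method is a survival analysis. A child whose first puff came before baseline has no time at risk, and a standard model may simply give that child no place in the risk set. The all-children sentence may be a general statement of analysis as randomised. It refers to hypotheses in the plural, and the second, on anti-smoking socialization, can be tested in ever smokers. The article also reports the 80 openly. They may have entered innocently, since mothers were interviewed first to check eligibility and children a few days later, although the text does not say so.

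Much of this stands, and it limits what may be claimed:

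- A reader might infer that the trial intends to count 80 earlier puffs as outcomes. The article does not state how they are coded, so that is not supported.
- A reader might infer that an uneven split biases the trial. Allocation followed baseline, so a chance imbalance is random error and not systematic bias.
- A reader might take the gap in ever-smoker shares for a 30/50 split, 50/750 − 30/729 = 2.6 points, as the shift in the result. Some of the children they displace would have had events, so the shift is about 2 points.
- A reader might infer that the trial loses adequate power. At the plan's own rates it does not.

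The defence does not remove the contradiction. If the survival model drops the 80, the written rule is broken without being amended; if they are kept as non-events, nothing drops them. Nor is this detail that an article leaves to a fuller document: the article does state an analysis population, and that population conflicts with its own criterion and outcome.

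**Conclusion.** The point holds as an inconsistency in the primary analysis set. Eligibility, the all-randomised rule and the definition of the primary event cannot all be followed for 80 of 1479 children. The consequence is modest in size: about half a point off a 10-point difference, and roughly 2 points of extra random error under an uneven split coded as events.

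This rests on an absolute 10-point effect with 30% in controls applied to never smokers, a proportional split unless stated otherwise, total inflation between 1 and 2, and reading the 80 as ever smokers at baseline. It should be settled before the initiation outcome is analysed, because it decides who is in that analysis.

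**What to change.** Reconcile Eligibility Criteria, Sample Size Calculation and Statistical analyses as follows.

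- Define the primary initiation analysis set as all randomised children who were never smokers at baseline (1399), analysed by allocated arm.
- Limit the all-children sentence to outcomes defined for every child, such as anti-smoking socialization, and say that this is where the 80 contribute. The susceptibility model is already limited and needs no change.
- State how the 80 came to be enrolled against the criterion, and whether the mother's or the child's baseline report decides smoking status, since Table 1 collects both.

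Because smoking status is recorded at baseline and allocation followed the baseline assessment, the restriction preserves the randomised comparison. The cost is wording and a nominal 1399 in place of 1479. That is still 1399 − 856 = 543 above the stated requirement, and no information on initiation is lost, since the 80 carry none.
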